### Participants’ recruitment

At the time of enrollment, after informed consent, subjects will visit the Unité d'Exploration en Nutrition (UEN) center twice or three times, first for a screening visit, a second visit to collect stool samples and complete questionnaires, and a third visit, only for 3 subjects, 12–18 months after the first stool collection as described below (Fig. 2).

**Fig. 2 fig0002:**
[figure not shown]
Flow Chart of the participant selection process in the iTARGET study.

To take part of the study, volunteers must complete the participant journey and collect a compliant stool sample. The study will be carried out in two phases. In the first phase (T0), stools from healthy participants will be collected, with a diversified diet rich in fiber, validated by a questionnaire carried out during the selection visit. Each participant will make one stool donation. This collection will permit the identification of carriers for bacteria of interest in relation to their diet and the development of targeted culturomics tools. In a second phase (T0+1 year), individuals selected according to their microbial profiles (*n* = 3) obtained from shotgun metagenomics at T0 in relation to their diet and whose stools presented the bacteria of interest (Table 1) will be recalled for a new stool donation in order to carry out culturomics using tools designed during the first phase (Fig. 1).

### Screening of participants

Subjects will be recruited from the UEN - CRNH Auvergne volunteer's database (declared under the number N°1,080,650 to the "Comité National de l'Informatique et des Libertés", CNIL), by advertisement in the local media and on the CRNH website and the INRAE local media. Subjects will be screened by telephone calls, during which an initial explanation of the study and the protocol will be given. For interested individuals, the information note and consent form will be sent or given to them before the selection visit.

### Selection visit

During the selection visit, the protocol will be explained in detail to the subjects based on the information form by one of the investigators of the UEN center, who will obtain their written agreement by signing the consent form. The subjects will then have their anthropometric parameters measured, and will complete a health and physical activity questionnaires [42], and a Bristol scale form. An interview with a dietician will follow to check the dietary selection criteria, using a dietary questionnaire. If the volunteer is included, he or she will leave with stool collection kits for home sampling. They will also receive a 3-day dietary record and a Bristol scale form to be filled at the time of their stool donation.

### Stool collection visit

During this visit, the subjects will come back at the UEN center, they will provide stool samples they have collected at home and the completed questionnaires. The dietician will check the dietary record with the volunteer and collect the completed Bristol scale. The volunteer will be reminded that he or she may be contacted again for a second stool collection, approximately one year after the first collection, to allow time for the analyses to be carried out on the first stool samples.

### Final visit at 12–18 months for three selected subjects

Based on metagenomic analyses and dietary profiles of the samples from the first phase (T0), three subjects will be recalled for a new stool collection. The subjects will be selected based on their most distinct metagenomic profiles and the detection of the selected species of interest (Table 1). The selection criteria will be checked again for each selected volunteer. The participants will again complete the questionnaires used for recruitment. If the subjects still meet the selection criteria, new stool collection kits will be distributed to them.

Samples that do not pass the initial quality control (e.g. presence of identification data on tube, missing sample, broken tube, etc.) are flagged up and a new sampling is given. QC-validated samples are stored at −80 °C at the MetaGenoPolis-SAMBO BRC (Biological Resources Centre), which is ISO9001 certified and labelled GIS-IBiSA (CRB N°242), until further processing.

### Withdrawal

The participation to this research project is purely voluntary and the participants are free to withdraw the study by asking the investigators of the study at any time.

### Description of measures taken to reduce and avoid bias

Subjects will be included chronologically and successively as long as they meet the inclusion/non-inclusion criteria and have given their consent to participate. The attrition bias is restricted as the monocentric nature of the study, the small number of subjects and the expertise of the staff involved in the study will limit the number of missing data. Data will be entered into the eCRF on an ongoing basis.

### Data collection

No medical procedures will be performed on the participants included in this study and no foreseeable risks are associated with this research. Stool samples do not entail any risk under the intended conditions of use. The provided collection kits and instructions enable samples to be taken simply, quickly and hygienically. The constraints are related to the stool collection and the time spent on the questionnaires. After the volunteers have been fully informed, consent will be obtained and appropriate procedures will be implemented for the processing of personal data.

Data will be entered using the Skezia software (https://skezia.io/) via the eCRFs by everyone involved in the project who has secure access to the eCRF. The Nutrition Investigation Unit will be responsible for entering clinical data. The data will be the property of the study sponsor. Anonymized data may be exported to the study directors.

All the information required by the protocol will be recorded in observation notebooks and an explanation will be given for any missing data. The data relating to the study that will be collected in the observation notebook will be considered as source data (Table 2).

**Table 2 tbl0002:** Overview of the data collected for each enrolled volunteer.

	Selection visit	Stool collection visit	final visit for 3 volunteers
Participant characteristics (age, gender)	X		
Anthropometric measures (weight, height and BMI)	X		X
health questionnaire	X		X
diet questionnaire	X		X
3- days dietary record		X	X
bristol stool scale for usual stool consistency		X	
Bristol stool scale for the donated stool		X	X

### The 24-hour dietary recall (24HR)

A 24-hour recall was used as a nutritional research tool for assessing individual's dietary intake over the previous 24-hour [43]. It involved the interview of individuals by a dietician to obtain detailed information about all foods and beverages ingested, from midnight to midnight, though main meals (breakfast, lunch, dinner) and outside mealtimes, including portion sizes and preparation methods.

### Dietary questionnaire for fiber consumption and selection criteria assessment

Spontaneous dietary fiber intake referred to the fiber consumed through dietary choices without intervention. The first step in assessing fiber intake was to compile a list of consumed foods based on the 24-hour dietary recall. This information was cross-referenced with the French food composition table CIQUAL 2020 [44] database to obtain the fiber content of each food item. Spreadsheets were used to organize and calculate the total fiber intake. Portion sizes were estimated using photographs from a validated picture booklet [45]. These portions sizes were applied to the corresponding food recorded in dietary recall, ensuring accuracy in quantifying fiber intake. During this interview, the following dietary criteria were also checked: diversified diet, rich in fruit and vegetables and low in ultra-processed foods.

## 3-Days food record

Before stool donation, dietary intake was estimated by means of three-day food records completed by the participants [43]. To remind participants to record all foods consumed, a food record was used including eight meal occasions (before breakfast, breakfast, morning snacks, lunch, afternoon snacks, evening meal, evening snacks, night snacks) referring to the current day. Participants had a face-to-face training in advance for the completion of the food records. Additionally, participants received instructions about the level of details required to describe foods and amounts consumed, including the name of the food, preparation methods, recipes for mixed foods and portion sizes. Portion sizes were reported in household measures, based on pictures or measured in gram or milliliters. During the interview with a dietician, the food record was checked to ensure an adequate level of details in describing foods and food preparation methods. Subsequently, each ingredient or food was translated into nutrients by use of CIQUAL French food composition table [45]. From these records, dietary intakes (in energy, macro- and micronutrients) were obtained using Nutrilog dietary software (https://nutrilog.com/).

### Sample size

To determine the minimum number of individuals required to achieve the project's objectives, and to provide an initial justification for our positive selection approach based on fiber consumption, we used healthy individuals from a published French cohort [46], representative of the French population we will target in the iTARGET study. The minimum number of individuals required to guarantee the detection of a species at least once was calculated for the19 selected species of interest (Table 1) using a binomial distribution with a probability of ≥ 0.95. Using this methodology, it was calculated that 4.4 ± 6.3 individuals were required to detect one of the 19 bacterial species of interest in the high-fiber diet group at least one time, while it would require 12,8 ± 34,1 individuals in the low-fiber group. Taking into account the mean and standard deviation, a minimum of 10 individuals on a high-fiber diet is required to maximize the prevalence of each of the selected microbial species of interest (Table 1).

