## Abstract

Recent advances in the study of the gut microbiota has pointed to its under-utilized source of potentially beneficial bacteria, known as next generation probiotics, offering a promising avenue to restore or compensate impaired gut microbiota toward a healthy state. Aside from the difficulties to achieve in-lab adequate culture conditions, the use of beneficial bacterial isolates is also limited by their bioavailability in the donor itself. In the iTARGET study, we positively selected donors based on their diet enriched in fiber, that has been shown to increase the prevalence of bacterial species associated with health.

The iTARGET study is a monocenter, prospective, observational study of adults with healthy lifestyle and high daily fiber consumption. We aim to recruit individuals in two phases, the first one for all individuals that will permit the identification of carriers for bacteria of interest and the second phase for a subset of individuals to allow for culture and isolation of previously identified potentially beneficial bacteria. Our primary outcome is the isolation and culture of at least one potentially beneficial isolate. The secondary outcomes comprised the high throughput metagenomic profiles of the intestinal microbiota and the characterization of the cultured isolates.

The study was approved by the French Research Ethics Committees (Comité de Protection des Personnes Sud-Est I) under the National reference ID 2023-A01677–38. Study findings and results will be published in peer-reviewed Open Access journals. (Trial registration number on ClinicalTrials.gov: NCT06166810).

Specifications table

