### Data analysis and outcomes

Subjects will be included chronologically and successively as soon as they meet the inclusion criteria and have given their consent to participate. The monocentric nature of the study, the small number of subjects and the expertise of the UEN staff involved in the study will limit the number of missing data. Data will be collected using observation notebooks specific to the study, using the Skezia software with secure access (https://skezia.io/). The software allows quality control of the data and monitoring of modifications, with the date and name of the person who made the modifications.

Our primary outcome is the isolation and culture of at least one isolate of each species of interest, previously identified by metagenomic data analysis and literature review (Table 1). The metagenomic identification of additional bacterial species of interest will rely on the bioinformatical and biostatistical of the French Milieu Intérieur cohort [47] for which we have obtained the consortium's agreement for use within the strict framework of this project (see iTARGET in https://www.milieuinterieur.fr/en/about-us/collaborations/), and additional public shotgun metagenomic datasets [10].

The secondary outcomes will be to first obtain metagenomic profiles of the faecal microbiota using a high throughput shotgun sequencing strategy [48] in order to identify the participant carriers for bacteria of interest in relation to their dietary profiles [10,49,50]. Combined analysis of metagenomic data, health records and diet profiles will be performed under the R software (version 3.6) [51]. Second, we aim to acquire phenotypic and genetic and/or genomic characteristics of the isolates, including growth parameters, production of bacterial metabolites, general sugar metabolisms, 16S rDNA sequencing and functional potential through genome annotation. We will collect and characterize at least one strain per donor and per media for the selected species of interest (Table 1).

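### The minimum of 10 donors rests on per-species detection at 0.95; the plan's own mean and SD show that it secures neither each of the 19 species nor the primary outcome

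*Protocol article*

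**What the plan says.** All references are to the protocol article.

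- **Sample size.** The section sets out to find how many individuals the project needs to reach its objectives. "The minimum number of individuals required to guarantee the detection of a species at least once was calculated" for each of the 19 species in Table 1, "using a binomial distribution with a probability of ≥ 0.95". The result is that "4.4 ± 6.3 individuals were required to detect one of the 19 bacterial species of interest in the high-fiber diet group at least one time". The corresponding figure for low-fiber individuals is 12.8 ± 34.1. It concludes: "Taking into account the mean and standard deviation, a minimum of 10 individuals on a high-fiber diet is required", and ties that number to each of the selected species.
- **Data analysis and outcomes.** "Our primary outcome is the isolation and culture of at least one isolate of each species of interest", with reference to Table 1, which has 19 rows.
- **Abstract.** The primary outcome is given in a weaker form, a single potentially beneficial isolate. The abstract also describes "the second phase for a subset of individuals to allow for culture and isolation of previously identified potentially beneficial bacteria".
- **Participants' recruitment** and **Final visit at 12–18 months for three selected subjects.** First-phase stools serve to find carriers and develop the culture tools. Then "three subjects will be recalled for a new stool collection", on which the culture work is done. The three are chosen for distinct metagenomic profiles and for detection of the target species.

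**The concern.** The event that was sized is not the event that the study is meant to deliver. The 0.95 applies to finding one given species by sequencing. The outcomes section requires all 19 species, and requires each to be cultured. Averaging the 19 per-species requirements and adding one SD does not turn a per-species figure into a statement about every species: the rarest species sets the requirement, and an average hides it.

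A reader of the Sample size section would take it that 10 donors give about 95% assurance for each target species and make the primary outcome reachable. If that is not so, the study may fall short of its outcome as written for reasons that could be foreseen from the planning data.

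**Working it through.** **Inputs.** From Sample size: target 0.95 per species, 19 species, requirement 4.4 ± 6.3 in the high-fiber group, stated minimum 10. The 19 prevalences are not given. No culture-recovery rate is given.

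**1. The stated figure.** 4.4 + 6.3 = 10.7, which would round up to 11. The stated 10 is the same quantity rounded down.

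**2. Per-species formula.** A species with prevalence p needs n = ln(0.05) / ln(1 − p) donors, so p = 1 − 0.05^(1/n). Ten donors include a carrier with probability 1 − 0.05^(10/n). Ten donors reach 0.95 only if p ≥ 1 − 0.05^(1/10) = 0.259.

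**3. Can all 19 requirements be 10 or less?** For values between 1 and b with mean m, the sample SD is at most √[(b − m)(m − 1) × 19/18] (Bhatia-Davis inequality). With b = 10 and m = 4.4: √(5.6 × 3.4 × 19/18) = 4.5. The reported SD is 6.3, so at least one species needs more than 10 donors.

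**4. How many does it need?** Solving for the largest value: b ≥ 4.4 + 6.3² × (18/19) / 3.4 = 4.4 + 11.1 = 15.5, so 16 in whole numbers. If fractional values down to 0 were used, b ≥ 4.4 + 6.3² × (18/19) / 4.4 = 12.9, about 13. Both are lower bounds on the largest requirement.

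**5. Detection of that species in 10 donors.**
- n = 16: p = 1 − 0.05^(1/16) = 0.171, and detection is 1 − 0.05^(10/16) = 0.85. Since 15 donors do not suffice for such a species, p is below 1 − 0.05^(1/15) = 0.181, so detection is at most 1 − 0.05^(10/15) = 0.86.
- n = 13: 1 − 0.05^(10/13) = 0.90.

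The chance that all 19 are carried cannot exceed the chance for the rarest one. So it is capped at about 0.85 (0.90 with fractional values), however the species co-occur.

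**6. All 19 among 10 donors, with independence assumed.** Four assumed sets, each with mean 4.4 and SD 6.3, using the product over species of 1 − 0.05^(10/n):

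| Assumed requirements | P(all 19 carried by 10) | Expected number carried | P(all 19) in the best 3 of those 10 |
|---|---|---|---|
| 18 species at 3.0, one at 30.4 | 0.63 | 18.6 | 0.63 |
| 17 at 2.3, two at 22.3 | 0.55 | 18.5 | 0.55 |
| 16 at 1.7, three at 18.6 | 0.51 | 18.4 | 0.51 |
| Skewed (lognormal), 1.0 to 27.7 | 0.59 | 18.5 | 0.57 |

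A wider search over whole-number sets matching the stated mean and SD gave 0.50 to 0.65. The last column is from 20,000 simulated cohorts per set, taking the trio with the best coverage.

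**7. Culture.** The documents give no recovery rate, so a range is assumed. If all 19 were carried, per-species recovery of 0.99, 0.95, 0.90 or 0.80 would give P(all 19 isolated) = 0.99^19 = 0.83, 0.95^19 = 0.38, 0.90^19 = 0.14 or 0.80^19 = 0.014, again with independence.

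**The case against.** **The three donors are selected, not random.** A reader might infer that going from 10 donors to three destroys the coverage, since a trio taken without regard to carriage would hold all 19 species only rarely. The documents do not support that reading. Recall depends partly on detection of the target species, and the table shows that a trio chosen for coverage loses almost nothing against all ten. That trio is a best case, because distinct profiles also count, donors must still qualify, and the stool is new. Even so, random-trio figures do not describe this plan.

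**0.95 to the power 19.** A reader might also take 0.95^19 = 0.38 as the chance of detecting all 19. That would hold only if every species stood at exactly 0.95. With 10 donors and a mean requirement of 4.4, most species are well above 0.95 and a few are below it. In step 7 the same number appears only as the result of an assumed culture recovery of 0.95.

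**Ten is a minimum.** This stands. Enrolling more raises coverage: in the four sets, the same product gives about 0.75 to 0.78 at 15 donors and 0.86 to 0.89 at 20. But 10 is the number that the section presents as sufficient.

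**The abstract's outcome is much weaker.** This stands too. If a single isolate were the outcome, the shortfall over 19 species would not matter. It does not rescue the calculation, which sizes neither outcome and still links 10 to each species.

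**Isolation from first-phase stools is not excluded.** Samples are stored, and the stated aim is not limited to three people. The point does not depend on this: the cap in step 5 already applies to all ten donors.

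**No hypothesis test or estimate is at risk.** True. The defect is a planning claim that its own figures contradict.

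**Conclusion.** The point holds as headed. Without any independence assumption, the published 4.4 ± 6.3 shows that 10 donors leave at least one target species at about 0.85 (0.90 if fractional requirements were used), below the 0.95 criterion, and the chance that all 19 are carried can be no higher. With independence, that chance is about 0.5 to 0.65, although 18.4 to 18.6 of the 19 would be expected among the ten donors. Coverage of most species is therefore good; coverage of every species is not secured.

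The primary outcome in Data analysis and outcomes is harder again, by an amount that the documents do not allow anyone to calculate, because culture recovery is left out. The gap between detection and culture and the step-5 bound are firm. The 0.5 to 0.65 and the culture figures rest on assumed prevalence sets, independence and assumed recovery rates.

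**What to change.** 1. Reconcile the primary outcome between the Abstract (at least one isolate) and Data analysis and outcomes (at least one of each species). Adequacy cannot be judged until this is settled.
2. From the 19 prevalences already held, replace the mean-plus-SD argument with what 10 donors deliver: the detection probability for each species including the rarest, the probability that all 19 are carried, and the expected number of the 19 carried by the three recalled donors under the planned selection.
3. Add culture recovery as an explicit assumption with a range, and carry it through to the expected number of species isolated.
4. Drop the statement that 10 donors meet the objectives or secure each species at 0.95.

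The cost is a short calculation on existing data and a rewritten paragraph. The stated figure will look less favourable. No extra enrolment is needed.

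### The reported 4.4 ± 6.3 donors per species cannot be reconciled with 10 donors serving each of the 19 species: at least one species must need 17 to 30

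*Protocol article*

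**What the plan says.** The Sample size section of the protocol article uses healthy people from a published French cohort. It defines the quantity to be sized as "The minimum number of individuals required to guarantee the detection of a species at least once", obtained for the 19 species in Table 1 "using a binomial distribution with a probability of ≥ 0.95". The result is a mean and SD over species: "it was calculated that 4.4 ± 6.3 individuals were required to detect one of the 19 bacterial species of interest" in the high-fiber group. The low-fiber figure, 12.8 ± 34.1, is given for contrast. The section then concludes: "Taking into account the mean and standard deviation, a minimum of 10 individuals on a high-fiber diet is required". That sentence names each selected species as the target and describes the aim as maximising prevalence.

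The section Data analysis and outcomes also works species by species: the primary outcome there is at least one cultured isolate of every species of interest. No other donor number is given for the first phase.

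**The concern.** A requirement worked out separately for 19 species has been reduced to a mean and SD, and a single number taken from that summary is then said to serve each species. To serve each species, the number must reach the largest of the 19 requirements. A mean and SD do not show that value, least of all when the SD exceeds the mean, as it does here for counts that cannot fall below 1. Such a set must have a long upper tail, and the species in that tail are the rare ones.

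At stake is the only numerical basis that the article gives for the number of donors. Phase-two donors are recalled partly because target species were detected in their first stool. A species with no detected carrier in phase one therefore cannot guide that choice.

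**Working it through.** **Inputs (all from the Sample size section).** 19 species; required donors per species n with mean 4.4 and SD 6.3; detection criterion 0.95; stated minimum 10. The ± figure is taken as the SD across the 19 species, since the section itself calls it a standard deviation. Each n is taken as a whole number of at least 1.

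**1. The plan's own figure.** The text does not say how the mean and SD lead to 10. The nearest simple rule is mean + SD = 4.4 + 6.3 = 10.7. Others are further away: mean + 2 SD = 17.0, and mean + 1.96 SD/√19 = 7.2. So 10 is close to mean + 1 SD, but that is an inference.

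**2. Could all 19 requirements be 10 or less?** For values between a and b with mean m, the variance (divisor k) is at most (b − m)(m − a). With a = 1, b = 10, m = 4.4, k = 19, the largest sample SD is

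√[(10 − 4.4)(4.4 − 1) × 19/18] = √(5.6 × 3.4 × 1.0556) = 4.48.

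Allowing values down to 0, it is √(5.6 × 4.4 × 1.0556) = 5.10. The reported SD is 6.3, so at least one species needs more than 10 donors.

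**3. How large must the largest requirement be?** Solving the same inequality for b with the sample SD:

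b ≥ 4.4 + 6.3² × (18/19)/(4.4 − 1) = 4.4 + 37.60/3.4 = 15.5.

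The upper limit is m + SD × (k − 1)/√k = 4.4 + 6.3 × 18/√19 = 30.4.

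These bounds treat n as continuous and may not be attained. Enumerating every set of 19 whole numbers of at least 1 whose mean and SD round to 4.4 and 6.3 gives:

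| SD definition | Largest requirement | Species needing more than 10 |
|---|---|---|
| Sample (divisor 18) | 17 to 30 | 1 to 5 |
| Population (divisor 19) | 17 to 31 | 1 to 5 |

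An example with five species above 10 is fourteen 1s plus 11, 11, 12, 14 and 22. The sum is 84, the mean 4.42 and the sample SD 6.27.

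**4. What 10 donors give the hardest species.** A species needing n donors has prevalence p with 1 − 0.05^(1/n) ≤ p < 1 − 0.05^(1/(n−1)). Detection in 10 donors is 1 − (1 − p)^10.

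| Required n | Prevalence p | Detection with 10 donors |
|---|---|---|
| 17 | 0.162 to 0.171 | 0.828 to 0.846 |
| 30 | 0.095 to 0.098 | 0.632 to 0.644 |
| 31 | 0.092 to 0.095 | 0.620 to 0.632 |

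**5. Where 10 donors do reach 0.95.** p ≥ 1 − 0.05^(1/10) = 0.259, that is, species carried by at least 25.9% of donors.

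**6. Sensitivity.** If unrounded requirements down to 0 had been averaged, the lower bound on the largest, allowing for rounding of 4.4 and 6.3, is about 12.8, or at least 13 donors. Detection with 10 would then be at most 0.918, still below 0.95.

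**The case against.** Several points can be made for the plan.

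- **The sentence with 10 does not repeat 0.95.** True. The probability is attached to the per-species calculation, and the conclusion speaks only of maximising prevalence for each species. The 0.95-for-each reading is therefore partly inferred. It is nevertheless the natural one: the 0.95 requirements are the only input to the 10, and the sentence names each species.
- **10 is a minimum.** Also true, and no upper limit on enrolment is stated. A reader might infer that only 10 donors will be recruited, or that the primary outcome will therefore be missed. The article supports neither. Three donors are recalled for the second-phase culture work, so the phase-one count does not by itself decide whether isolates are obtained. What fails is the statement that 10 is the number that serves each species.
- **The Abstract asks for only one isolate.** It does state the primary outcome that way, but the Sample size section sets its own target as each species and must be judged against that.
- **The article is condensed.** The 19 individual values may stand in the full protocol, and their absence here is no fault. The point is that the published mean and SD contradict the published conclusion, whatever the individual values are.

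A reader might also say that 10 should simply be 11, because 4.4 + 6.3 = 10.7. The text states neither a mean + 1 SD formula nor a rounding rule, and 11 would still fall short of the hardest species. That correction is not supported.

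**Conclusion.** Wrong as written. The reported mean and SD rule out 10 donors as sufficient for 0.95 detection of each of the 19 species. The hardest species needs 17 to 30 donors (31 with the population SD), and between one and five species need more than 10. With 10 donors, detection of the hardest species is about 0.62 to 0.85.

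This rests on the ± figure being the SD across the 19 per-species requirements, and on those being whole numbers of at least 1. Relaxing the second assumption lowers the bound to 13 donors and leaves the conclusion unchanged. Which species are affected, and the exact largest requirement, cannot be known from the article.

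The reference to maximising prevalence is a separate wording error: the number of donors does not change how common a species is, only the chance of finding it. The consequence is an overstated sample-size claim in an observational study that states no hypothesis test, not a demonstrated failure of the study.

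**What to change.** Rewrite the closing sentences of the Sample size section in one of two ways.

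1. **Keep the claim for each species.** Set the minimum at the largest of the 19 per-species requirements already computed, and state that value. This may mean recruiting more than 10 donors.
2. **Keep 10 donors.** State that 0.95 detection holds only for species with prevalence of about 26% or more in the high-fiber group. Name the species below that, each with its detection probability in 10 donors, 1 − (1 − p)^10.

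In either case, replace the wording about maximising prevalence with wording about the probability of detecting each species at least once.

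The cost is one rewritten paragraph based on values that the sponsor already has. The second option needs no added recruitment; its price is a less favourable stated figure.
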